## Abstract

**Background:**

Dyslipidemia is a major risk factor for atherosclerotic cardiovascular disease and a leading cause of death worldwide. The clinical utility of commonly used lipid-lowering drugs such as statins and fibrates is sometimes limited by the occurrence of various adverse reactions. Recently, berberine (BBR) has received increasing attention as a safer and more cost-effective option to manage dyslipidemia. Thus, a high-quality randomized controlled trial to evaluate the efficacy and safety of BBR in the treatment of dyslipidemia is deemed necessary.

**Methods/design:**

This is a randomized, double-blind, and placebo-controlled clinical trial. A total of 118 patients with dyslipidemia will be enrolled in this study and randomized into two groups at a ratio of 1:1. BBR or placebo will be taken orally for 12 weeks. The primary outcome is the percentage of low-density lipoprotein cholesterol reduction at week 12. Other outcome measures include changes in other lipid profiles, high sensitivity C-reactive protein, blood pressure, body weight, Bristol Stool Chart, traditional Chinese medicine symptom form, adipokine profiles, and metagenomics of intestinal microbiota. Safety assessment includes general physical examination, blood and urine routine test, liver and kidney function test, and adverse events.

**Discussion:**

This trial may provide high-quality evidence on the efficacy and safety of BBR for dyslipidemia. Importantly, the findings of this trial will help to identify patient and disease characteristics that may predict favorable outcomes of treatment with BBR and optimize its indication for clinical use.

**Trial registration:**

Chinese Clinical Trial Registry ChiCTR1900021361. Registered on 17 February 2019.

**Supplementary Information:**

The online version contains supplementary material available at 10.1186/s13063-021-05028-8.

## Background

Dyslipidemia is characterized by increased plasma total cholesterol (TC), low-density lipoprotein cholesterol (LDL-C), triglyceride (TG), or decreased high-density lipoprotein cholesterol (HDL-C). It is the main risk factor correlated with the occurrence and progression of atherosclerosis, cardiovascular disease (CVD), and stroke [1, 2]. As CVD remains a major cause of morbidity and mortality globally, the management of dyslipidemia is a key component of primary and secondary risk reduction strategies [3]. Statins, as the first-line therapy for dyslipidemia recommended by international clinical practice guidelines, can significantly reduce the risk of cardiovascular events [4, 5]. Nevertheless, statins are also associated with various adverse reactions such as hepatobiliary disorders, renal disease, myalgia, myositis, and rhabdomyolysis; long-term use of statins may increase the risk of incipient diabetes and cognitive dysfunction [6–11]. Other drugs such as fibrates also have similar adverse reactions, including liver toxicity, renal toxicity, and myopathy [12]. The management of dyslipidemia still remains a major challenge for patients who cannot tolerate the side effects of these classic lipid-lowering drugs (LLDs). Therefore, it is important to seek effective and safe alternatives to these LLDs.

Berberine (BBR) is an isoquinoline alkaloid isolated from various Chinese herbs, including Rhizoma coptidis (huanglian), Cortex phellodendri (huangbai), and Hydrastiscanadensis (goldenseal) [13]. It was initially used for the treatment of gastrointestinal infection. In recent years, a number of studies have suggested that BBR has a variety of pharmacological properties, such as antibacterial, antitumor, controlling arrhythmia, lowering blood lipids, lowering blood pressure, lowering blood glucose, and promoting islet cell regeneration [14–18].

The lipid-lowering effect of BBR has been supported in several studies. Kong et al. [17] reported that compared with placebo, oral BBR 0.5 g twice daily reduced the serum TC by 29%, TG by 35%, and LDL-C by 25%. Moreover, BBR combined with simvastatin showed enhanced lipid-lowering effect compared with monotherapy: the serum LDL-C was reduced by 31.8%, and reductions in TC and TG were also observed [19].

Occasionally, oral or intravenous BBR may cause adverse reactions such as nausea, vomiting, constipation, hypertension, respiratory failure, and paresthesias. Rare adverse effects including headache, skin irritation, facial flushing, headache, and bradycardia have also been reported [20]. The therapeutic dose of BBR (0.5 g) is generally safe and well-tolerated, and gastrointestinal reactions are most often caused by overdose (≥ 4 g).

A recent systematic review and meta-analysis demonstrated that BBR could significantly reduce the levels of TC, LDL-C, and TG in patients with dyslipidemia [13]. Unfortunately, these studies were limited by their high heterogeneity and high risk of biases. Kong et al. [17] proved that BBR treatment significantly improved lipid profiles; however, the randomization, blinding procedure, sample size calculation, and detailed inclusion and exclusion criteria have not been mentioned, and a lack of restriction on the other medications could have influenced the results. As there has been a lack of large-scale, high-quality randomized controlled trials on this possibility at the population level, this randomized, double-blind, placebo-controlled clinical trial was designed to determine the lipid-lowering efficacy and safety of BBR in treating dyslipidemia.

## Methods/design

### Trial objective

The objectives of this trial are as follows:
To assess the efficacy and safety of BBR for dyslipidemiaTo identify patient and disease characteristics that may predict favorable outcomes of treatment with BBR and optimize its indication for clinical use

### Design

This is a study protocol for a randomized, double-blind, placebo-controlled clinical trial with a treatment period of 12 weeks, which will be conducted between April 2019 and December 2020. Eligible patients will be randomized at a ratio of 1:1 into either the BBR group or the placebo group. The protocol was developed according to Consolidated Standards of Reporting Trials (CONSORT) statement [21], Standard Protocol Items: Recommendations for Interventional Trials (SPIRIT) 2013 [22], and SPIRIT 2013 explanation and elaboration: guidance for protocols of clinical trials [23]. A total of 4 visits will be scheduled at baseline (visit 1) and weeks 4 (visit 2), 8 (visit 3), and 12 (visit 4) to assess treatment efficacy, safety, and adverse events. This 12-week treatment period was set based on our clinical experience and previous pilot studies [13, 17]. Additionally, potential predictive factors involving patient and disease characteristics have been collected in a comprehensive manner. Figure 1 shows the flow diagram of the trial.

**Fig. 1 Fig1:**
[figure not shown]
Study flowchart. BBR, berberine

The protocol design is based on the Standard Protocol Items: Recommendations for Interventional Trials (SPIRIT) Checklist (Additional file 1).

### Institutional setting

This study will be conducted in Dongzhimen Hospital Affiliated to Beijing University of Chinese Medicine (DHABUCM), Beijing, China.

### Recruitment and participants

#### Recruitment procedures

All participants will be recruited in DHABUCM. Advertisements and colored fliers will also be placed inside the hospital. The contents of the recruitment advertisement include a brief introduction to dyslipidemia and BBR, the inclusion criteria, the intervention, and the contact information of the investigators. Those who are willing to participate in this trial may contact the research assistants by telephone. Once they have volunteered to participate, they will be assessed according to the inclusion and exclusion criteria. Eligible patients will be asked to sign the written informed consent form before the initiation of any study-related procedures. The detailed information about the participants will never be revealed to any individual or organization relevant to the study.

### Research population and inclusion criteria

#### Diagnostic criteria

The diagnosis of dyslipidemia is made according to the Guidelines for the Prevention and Treatment of Dyslipidemia in Chinese Adults (revised in 2016) [24]: TC ≥ 6.2 mmol/L or LDL-C ≥ 4.1 mmol/L or HDL-C < 1.0 mmol/L or TG ≥ 2.3 mmol/L, occurring in the absence of any secondary causes.

#### Inclusion criteria

Diagnosis of primary dyslipidemiaLDL-C ≥ 4.1 mmol/L and/or TG ≥ 2.3 mmol/LAge between 18 and 70 years, male or femaleHaving not taken any LLDs within the past 1 monthAble to adhere to long-term treatmentHaving voluntarily given their informed consent

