#### Randomization

The stratified blocked randomization method will be used. The statistical software SAS 9.2 (SAS Institute Inc., Cary, USA) will be used by an independent statistician who is not involved in the implementation or statistical analysis of the trial. A random code list will be generated, and eligible participants will be randomly assigned to either the BBR group or the placebo group at a ratio of 1:1.

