### Outcomes

#### Primary outcome

The primary outcome is the percentage change in LDL-C from baseline at week 12.

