#### Sample size calculation

The sample size for this trial was calculated based on the primary outcome using the PASS 11.0 (NCSS LLC, Kaysville, UT, USA) software. According to the previous results of berberine on dyslipidemia [17, 26], the percentage reduction in LDL-C (the primary outcome) is 25% in the berberine group and 5% in the placebo group. Forty-seven patients in each group can achieve 80% power and rule out type I error of 5% by using a two-sided test. We expect that 20% of the participants may be lost to follow-up. Therefore, the sample size in each group should be adjusted to 59. In total, 118 participants will be enrolled in this trial.

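### Patients can enter on triglycerides alone while the primary outcome is LDL-C change, and the stated primary comparison takes no account of baseline LDL-C or entry type

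*Protocol article*

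**What the plan says.** All references are to the protocol article.

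- **Inclusion criteria.** The LDL-C threshold (4.1 mmol/L) and the TG threshold (2.3 mmol/L) are linked by "mmol/L and/or TG". Either one is enough for entry.
- **Primary outcome.** "The primary outcome is the percentage change in LDL-C from baseline at week 12". It applies to every randomised patient, whichever threshold brought them in.
- **Sample size calculation.** One effect is used for the whole sample: "the percentage reduction in LDL-C (the primary outcome) is 25% in the berberine group and 5% in the placebo group".
- **Randomization.** "The stratified blocked randomization method will be used", at 1:1. No stratification factor is named.
- **Statistical analysis.** Continuous variables are compared between arms at each time point with Student's t test or the Wilcoxon-Mann-Whitney test. Neither contains a term for baseline LDL-C or lipid type.
- **Trial objective.** The first aim is efficacy and safety in dyslipidemia generally. The second is to find patient and disease characteristics that predict a good response.

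**The concern.** The entry rule creates two groups that differ, by definition, on the baseline value of the outcome variable: patients at or above 4.1 mmol/L LDL-C, and patients below it who qualify on TG. The named test pools them and ignores the difference. Three things follow.

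1. The primary estimate is an average whose weights depend on how many TG-only patients enrol. The article does not cap that share.
2. If baseline LDL-C predicts percentage change in LDL-C, an unadjusted test has a larger standard error than necessary.
3. The arms may differ by chance in lipid type, and the stated analysis does not correct for it.

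Entry status is also an obvious candidate predictor under the trial's second objective, yet the article describes no analysis by it. A reader wanting to know what berberine does to LDL-C in patients whose LDL-C is raised would not get the answer from the primary result alone.

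**Working it through.** **1. The plan's own figure.** Inputs from Sample size calculation: 25% against 5%, two-sided 5%, 80% power, 20% loss. The two-proportion formula with unpooled variance gives

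n = (1.960 + 0.842)² × (0.25×0.75 + 0.05×0.95) / 0.20² = 46.1, rounded up to 47 per arm.

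Then 47 / 0.80 = 58.75, so 59 per arm and 118 in total. The stated figures reproduce. No SD enters, and the article gives none.

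**2. What the average could be.** Let q be the share of TG-only entrants and r the fraction of the 20-point effect they receive. Neither is in the article; both are assumed here. It is also assumed that the 20 points apply to patients at or above 4.1 mmol/L.

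Overall difference = 20 × [(1 − q) + q·r]

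| q | r = 0 | r = 0.5 | r = 1 |
|---|---|---|---|
| 0.25 | 15 | 17.5 | 20 |
| 0.50 | 10 | 15 | 20 |
| 0.75 | 5 | 12.5 | 20 |

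The last column matters. The outcome is a percentage of each patient's own baseline, so an equal percentage effect in both groups is possible, and then nothing is diluted.

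**3. Precision.** In a randomised comparison, adjusting for baseline multiplies the residual variance by about 1 − ρ², where ρ is the within-arm correlation between baseline LDL-C and percentage change. ρ is not given. Assumed values: 0.1 gives 0.99, 0.3 gives 0.91, 0.5 gives 0.75. The gain runs from negligible to a quarter of the variance.

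**4. Chance imbalance.** If lipid type is not a stratification factor, the between-arm difference in TG-only share with 59 per arm has standard error √[2q(1 − q)/59].

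- q = 0.25: √(0.375/59) = 0.080, 95% range ±16 percentage points.
- q = 0.50: √(0.5/59) = 0.092, 95% range ±18 percentage points.

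Suppose LDL-C change differs between the two types by 5 to 10 points regardless of treatment (assumed). An imbalance at the edge of that range then moves the estimate by 0.16×5 = 0.8 to 0.18×10 = 1.8 points. That is small against 20, and adjustment removes it.

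**5. What the interaction test can do.** Assume SD 20, 59 per arm, and an effect of 5 or 10 points in TG-only patients against 20 in the others, so an interaction of 15 or 10 points.

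SE = 20 × √[2/(59(1 − q)) + 2/(59q)]

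- q = 0.50: SE 7.4; power about 53% for 15 points, 27% for 10.
- q = 0.25: SE 8.5; power about 42% and 22%.

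A larger SD lowers all four.

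**6. What the subgroup intervals would look like.** With the same assumed SD of 20 and q = 0.25, the 95% half-width is 1.96×20×√(2/44.25) = 8.3 points in the group at or above 4.1 mmol/L and 1.96×20×√(2/14.75) = 14.4 points in the TG-only group. Overall it is 1.96×20×√(2/59) = 7.2.

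**The case against.** The trial aims at dyslipidemia, which the article defines to include raised TG. Randomisation makes the comparison valid for the population enrolled, and averaging over it is not bias. This stands.

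A reader might go further and infer any of four things that the article does not support.

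- *That TG-only entrants have normal LDL-C.* They have LDL-C below 4.1 mmol/L, possibly only just below.
- *That the randomisation strata fail to protect the comparison.* No factor is named. Lipid type could be one, and an article may leave that detail to the full protocol. Stratifying would balance the arms but would not change the mix or the averaging.
- *That the effect is diluted.* Nothing in the article says the percentage effect is smaller below 4.1 mmol/L. The 25% and 5% come from cited work in dyslipidemia, and the article does not say who was in it; they may already describe a mixed population.
- *That power is badly short.* Such a figure needs an SD. Back-solving one from 47 per arm gives about 34 points, but 47 comes from a formula for proportions, so that SD is an artefact and not a planning value.

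It can also be said that covariates and subgroups belong in the analysis plan, which is not shown. That would answer the point if the article were silent, but it names the between-group tests and they are unadjusted. If the analysis plan already adjusts for baseline LDL-C and reports by entry status, the sponsor need only confirm it.

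**Conclusion.** The point holds as a modest, inexpensive improvement to a stated method, not as a flaw that invalidates the trial. The article fixes three things that fit together poorly: entry on TG alone, an LDL-C primary outcome for all, and an unadjusted two-group test.

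The cost of leaving it is a primary estimate whose population weights are uncontrolled, an unknown loss of precision (0% to 25% of the variance for assumed ρ from 0 to 0.5), and uncorrected chance imbalance worth about 1 to 2 points under the assumptions above. The size of any dilution cannot be determined from the article. The 5-to-20-point range shows only how much depends on quantities not given, and its upper end is no dilution at all.

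**What to change.** Before unblinding, in the analysis plan:

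1. Analyse the primary outcome by ANCOVA with treatment and baseline LDL-C as terms, or with entry status (at or above against below 4.1 mmol/L) as the covariate instead. State which one.
2. Pre-specify the treatment difference in percentage LDL-C change, with a 95% confidence interval, in each entry group. Show the group at or above 4.1 mmol/L beside the overall result.
3. Report the number of TG-only entrants per arm.
4. Label the treatment-by-entry-status interaction test exploratory. Its power is low, and a non-significant result must not be read as evidence of equal effects.

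The overall comparison stays primary. Eligibility, sample size and the randomisation list stay as they are. Recruitment is under way according to Trial status, so a new stratification factor is not proposed. Baseline LDL-C is already collected at visit 1.

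The cost is a few lines of text and a little more analysis. The subgroup estimates will be imprecise, most of all in the smaller entry group.

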#### Exclusion criteria

History of myocardial infarction, stenting, bypass surgery, or stroke within the past 4 weeksCombined with diabetes, nephrotic syndrome, or renal insufficiencyCombined with poorly controlled hypothyroidism or other endocrine diseasesAlanine aminotransferase (ALT) and/or aspartate aminotransferase (AST) ≥ 2 times the upper limit of normalCombined with severe or active liver diseasesCombined with severe or any other life-threatening diseaseAllergy to components of the product or allergic constitutionCombined with a mental disorderParticipated in clinical trials of other drugs in the past 4 weeks

#### Randomization

The stratified blocked randomization method will be used. The statistical software SAS 9.2 (SAS Institute Inc., Cary, USA) will be used by an independent statistician who is not involved in the implementation or statistical analysis of the trial. A random code list will be generated, and eligible participants will be randomly assigned to either the BBR group or the placebo group at a ratio of 1:1.

#### Blinding and unblinding procedures

A two-level blinding design will be used, with the first level being by group (group A and group B) according to case number and the second level by treatment (BBR and placebo).

The random code list will be created by a statistical agency, the two-level treatment codes will be sealed separately in duplicate, with a copy being kept by DHABUCM and the National Drug Clinical Trial Institution. Treatment allocations will be blinded to the participants, clinicians, research assistants, drug managers, statisticians, and other staff members and will not be revealed until the study is completed. The study would have been considered invalid if any treatment code disclosure arose from any non-prescribed circumstances and if it affected the objectivity of the data obtained from the study.

Whether the drug packaging meets the requirements of a double-blind clinical trial will be checked, and the drug quality inspection report will be created. The entire drug coding process is documented by the blind editor, as part of the documentation for the clinical trial. Each coded test drug will have a corresponding emergency letter, describing the subject’s medication, treatment methods, organization, and address to which requests for emergency unblinding should be immediately reported. The coded drugs will be sent to the study center together with the corresponding emergency letters.

In case of emergency (such as serious adverse reactions), or when the patient needs to be rescued and must know what kind of treatment the patient has received, the corresponding emergency letters shall be opened with the presence of the investigators and the administrator of research organization. Once the emergency letter is opened, the numbered subject will withdraw from the study. The investigators will record the reason in the case report form (CRF). All emergency letters will be collected with the CRFs for blind review at the end of the trial.

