#### Secondary outcomes

The following are the secondary outcomes:
Lipid profiles: TC, TG, HDL-C, and LDL-C will be measured at baseline (visit 1) and weeks 4 (visit 2), 8 (visit 3), and 12 (visit 4).Hs-CRP, BP, and body weight will be measured at baseline (visit 1) and weeks 4 (visit 2), 8 (visit 3), and 12 (visit 4).BSC: the participants will be asked “which type of stool they have” at each visit during the treatment period.TCM symptom form (according to the Clinical Research Guidance of New Investigational Drug in TCM [25]) will be evaluated at baseline (visit 1) and weeks 4 (visit 2), 8 (visit 3), and 12 (visit 4).Adipokine profiles [fibroblast growth factor 21 (FGF21), adiponectin (APN), hormone-sensitive lipase (HSL)] will be assessed based on the blood specimens collected at baseline (visit 1) and week 12 (visit 4).Intestinal microbiota will be analyzed by the metagenomics based on the stool specimens collected at baseline (visit 1) and week 12 (visit 4).

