#### Adverse event monitoring

When a serious adverse event happens, investigators must fill out the “SAE form” and report it to the major investigator and center ethics committee immediately. The event should be reported to the safety supervision division of the State Food and Drug Administration within 24 h.

The major investigator must offer corresponding treatment according to the drugs and symptoms, then record and sign at the CRFs in detail. The inspector must be informed of the treating processes.

All adverse events should be recorded in time and tracked until properly resolved or stabilized. Abnormal indexes in physical and chemical examinations should be checked until normal.

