**Safety assessment**				
Blood routine measurements	√			√
Urine routine measurements	√			√
Liver function (ALT, AST)	√			√
Kidney function (BUN, Cr)	√			√
Adverse events	√	√	√	√

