#### Statistical analysis

Statistical analysis of all data will be performed by a dedicated statistician in a blinded manner. All statistical analyses of the data will be performed using the SAS 6.12 (SAS Institute Inc., Cary, NC, USA) software.

The analysis data set will consist of a full analysis set (FAS), a per-protocol set (PPS), and a safety set (SS). FAS: according to the principle of analysis for intention to treat (ITT), participants will be rejected by the smallest and reasonable method. The last observation carried forward (LOCF) method will be used for the missing data supplement. The PP data set will include only participants who adhered to the study protocol and completed the clinical study. The minimum compliance rate for participants taking the investigational drugs in the PP data set is 80%. The SS will include information on safety records, including adverse events and laboratory test results. Quantitative indices recorded will include the numbers of cases, mean ± SD, median, and maximum and minimum values; qualitative or grade indices will be recorded using frequency and percentage. Two-sided tests will be used in all cases, and *P* ≤ 0.05 will be considered to be statistically significant.

From baseline to each time point, discrete variables will be described with frequencies and percentages, and continuous variables will be described with either mean and standard deviation for data with normal distribution or median and interquartile range for non-normally distributed data. For comparisons between the experimental and control groups at each time point, a chi-square test or Fisher’s exact test will be used for discrete variables, and Student’s *t* test or the Wilcoxon-Mann-Whitney *U* test will be used for continuous variables.

The analysis of concomitant medications will be analyzed by the chi-square test or Fisher’s exact test. The analysis of treatment compliance should include both the experimental drug and the basic treatment, and the chi-square test/Fisher exact probability method will be used for comparison.

All adverse events during the trial should be described in the form with the type, severity, and relationship with the experimental drug. Adverse events will be classified into all adverse events and related adverse events, among which, for conservative consideration, will include “definitely related,” “probably related,” “possibly related,” and “suspected related” to the drug.

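### Emergency unblinding ends study participation, so a participant unblinded before week 12 has no week-12 LDL-C and no scheduled post-baseline safety laboratory result

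*Protocol article*

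**What the plan says.** All references are to the protocol article.

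- **Blinding and unblinding procedures.** The letter may be opened "In case of emergency (such as serious adverse reactions), or when the patient needs to be rescued" and the treatment must be known. The consequence follows directly: "Once the emergency letter is opened, the numbered subject will withdraw from the study". The investigator records the reason in the case report form.
- **Primary outcome.** "The primary outcome is the percentage change in LDL-C from baseline at week 12". The secondary outcomes and Table 1 also schedule LDL-C at weeks 4 and 8.
- **Statistical analysis.** The full analysis set is formed as follows: "according to the principle of analysis for intention to treat (ITT), participants will be rejected by the smallest and reasonable method". For gaps, "The last observation carried forward (LOCF) method will be used for the missing data supplement". The safety set is to hold adverse events and laboratory results.
- **Table 1, safety assessment.** Blood routine, urine routine, liver function and kidney function are ticked at V1 and V4 only. Adverse events are ticked at every visit.
- **Adverse event monitoring.** "All adverse events should be recorded in time and tracked until properly resolved or stabilized". Abnormal test results are to be rechecked until normal. No exception is made for withdrawn participants, and continuation after withdrawal is not mentioned.

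**The concern.** Three things are being treated as one: breaking the blind, stopping study drug, and leaving the study. An emergency may require the first, and whether it requires the second is a clinical matter. Nothing in the stated reason for opening the letter requires the third, which is the one that removes data.

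The participants affected are selected by an event after randomization, usually a suspected serious reaction, so the resulting gaps are unlikely to be unrelated to treatment or outcome. For efficacy, an observed week-12 value is replaced by an earlier one. For safety, which is part of the first trial objective, the participants most likely to have an informative laboratory result are those for whom the schedule no longer provides one. An analysis plan cannot repair this later, because the measurements would not have been taken.

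**Working it through.** **1. The plan's own loss allowance.** 47 / (1 − 0.20) = 58.75, rounded up to 59 per group and 118 in total. The stated figures reproduce, and this point disputes none of them. The allowance is 59 − 47 = 12 per group.

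**2. What is lost, by time of unblinding.** This sets the unblinding rule beside Table 1 and the LOCF sentence.

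| Letter opened | Value used for week-12 LDL-C | Scheduled post-baseline safety laboratory result |
|---|---|---|
| Before week 4 visit | Baseline carried (0% change) | None |
| Between week 4 and week 8 visits | Week 4 value carried | None |
| Between week 8 and week 12 visits | Week 8 value carried | None |
| After the week 12 assessments | Observed | Present |

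In the first row LOCF records no response. In the next two it carries an earlier value to week 12 whatever LDL-C then did. The net direction of bias cannot be settled from the article.

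**3. How many participants.** The article gives no unblinding rate, so the rates here are assumptions. Expected number = rate × 118. Chance of at least one = 1 − (1 − rate)^118.

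| Assumed rate | Expected of 118 | Chance of at least one |
|---|---|---|
| 1% | 1.2 | 69% |
| 2% | 2.4 | 91% |
| 5% | 5.9 | 99.8% |

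The number is small, but the rule would probably be used at least once.

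**4. Effect on the primary comparison in an unfavourable case.** Put all *k* unblindings in the berberine group before week 4, so that LOCF carries 0% change. Hold the other berberine participants at the planned 25% reduction and placebo at 5%. Expected berberine reduction = 25 × (1 − *k*/59). Expected difference = that value − 5.

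| *k* of 59 | Berberine reduction | Difference (planned: 20 points) |
|---|---|---|
| 1 | 24.6% | 19.6 |
| 3 | 23.7% | 18.7 |
| 6 | 22.5% | 17.5 |

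These counts lie within the allowance of 12 per group. Power is not the main issue.

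**5. Effect on the safety laboratory data.** Each participant unblinded before week 12 removes 1/59 = 1.7% of that arm's scheduled week-12 panels, and six remove 6/59 = 10.2%. There is no scheduled week 4 or week 8 panel to fall back on.

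**6. The unblinding rule against adverse-event follow-up.** One section ends participation. The other requires tracking to resolution. They can be read together if follow-up outlasts withdrawal, but neither says so. Rechecking an abnormal test also presupposes that a test was done and found abnormal; it does not schedule one.

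**The case against.** The strongest reply is that little is lost. The letter is opened only in an emergency in which the treatment must be known. The background section describes the therapeutic dose as generally safe and well tolerated, and the exclusion criteria remove people with severe or active liver disease and other severe or life-threatening disease. The triggering event is still captured through serious adverse event reporting. The article also condenses a fuller protocol, which may describe an early-termination visit. Most of this stands: the number affected is probably small, and the absence of an early-termination visit from an article is not a fault. It does not answer the point, because the withdrawal rule is stated outright.

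A reader might draw four stronger conclusions that the documents do not support.

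- **That the rule breaches intention to treat.** Nothing removes unblinded participants from the full analysis set or safety set, and LOCF supplies a value. The defect is avoidable missing data, not exclusion.
- **That every patient with a serious reaction is lost.** Only those whose letter is opened before the week-12 assessments are affected.
- **That no post-baseline laboratory value could exist.** Only scheduled values are lost. Follow-up of events and of abnormal tests may produce unscheduled ones.
- **That about 24 of 118 participants are affected (0.20 × 118 = 23.6).** That is the general allowance for loss to follow-up. Early leavers for any reason miss the week-12 panel because of the Table 1 schedule, and rewording the unblinding rule would recover only those who left through unblinding.

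**Conclusion.** The point holds in a limited form. As written, the protocol turns emergency unblinding into the end of data collection. It thereby creates missing week-12 LDL-C and leaves no scheduled post-baseline safety laboratory result in a group selected by safety events. This supports the intention-to-treat principle poorly and leaves two sections unreconciled on follow-up.

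The size is uncertain. Under assumed rates of 1% to 5%, about 1 to 6 of 118 participants would be unblinded, with fewer affected if some letters are opened after the week-12 assessments. In the unfavourable case shown, the expected LDL-C difference falls from 20 to between 19.6 and 17.5 points. The reason to act is the safety record: with 59 per arm, a few serious reactions may be much of the safety signal. This is an inexpensive improvement to the protocol, not a flaw that invalidates the design.

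**What to change.** Reword the sentence in the blinding and unblinding section so that opening the letter is recorded, with date and reason, but does not by itself end data collection. Unless the participant withdraws consent, continue the remaining scheduled visits, including week-12 LDL-C and the week-12 blood, urine, liver and kidney tests. Add a sentence there or under adverse event monitoring stating that adverse events and abnormal tests are followed after unblinding in the same way as for other participants, so that the two sections agree. Treatment after unblinding is left to the clinicians, and this change takes no position on it.

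The visits and tests are already in Table 1, and the article provides an amendment route through the ethics committee. The downside is a few visits from participants who are no longer blinded. LDL-C and the safety panel are laboratory measurements and are less exposed to that than the symptom form or stool chart. Flag those visits in the data.
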